#### Secondary outcome

2.4.2

Secondary outcomes will be measured individually at 6 weeks and 3 and 6 months post treatment. Table 2 has provided the time points and specific measurements of data. The mainly secondary outcomes are as follows:(1)Uterine scar thickness and areaThe uterine scar thickness and area will be measured using a transvaginal utrasonography device.(2)Mother's milk and serum will be collected at each visit and the immunoglobulin (IgG, IgA, IgM) and the complement (C3, C4) will be detected by transmission immune turbidity method using automatic biochemical analyzer.

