### Randomization and masking

2.2

In total, 120 participants will be randomly assigned to 1 of 2 groups in a 1:1 ratio, the MSCs or placebo-controlled groups. Randomization numbers are completed by using the computer-generated list of random numbers. An independent statistician who is involved in neither the treatment nor data collection will randomize assignments in this study. It will be blinded to random allocation of participants to the 2 groups. The final group assignments will be sealed in opaque envelopes. Other than the investigational pharmacist who prepared the study drug, clinical and research staff members will be blinded in this trial. The assessors and statisticians for the data collection and analysis will be also blinded to the assignments.

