**Table 2 T2:**
[figure not shown]
Schedule of visits and assessments.

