### Adverse events

2.5

On the basis of clinical severity, all adverse events, including mild, moderate, and severe, will be obtained and recorded at baseline and throughout the 6-month follow-up. Every time when follow-up, the participants will come to the interviewing room where the case report form (CRF) with adverse events will be filled with their feedback and the specialist checks. We will focus on the wound infection, endometritis, or other infections occurring up to 6 months after delivery in both groups. To evaluate tumor formation as a delayed reaction, we will test the tumor markers (CA12–5, CA15–3, CA19–9, and carcinoembryonic antigen) at baseline and 6 months. The principal investigator (ZL) will be responsible for managing the adverse events clinically. All adverse events will be reported to the Adverse Events Monitoring Committee.

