### Statistical analysis

2.8

For data analysis, all analyses will be performed according to the intention-to-treat principle. Continuous data will be expressed as mean/standard deviation if it meets normal distribution, otherwise it will be presented by medians/interquartile range; categorical data will be expressed as frequency and percentage. In terms of comparison between the 2 groups, 2-tail Student *t* test for continuous data or the Chi-square test or Fisher exact test for categorical data will be used for outcomes. Relative risks and 95% confidence intervals will be calculated for outcomes. To assess changes of outcome levels over time, an analysis of variance (ANOVA) for repeated measures with post-hoc paired *t* tests or Wilcoxon signed rank test will be used for continuous data. Statistical significance is established at *P* < .05. Statistical analysis will be performed using R 3.0.3.

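### Section 2.4.2 names only post-treatment times for serum immunoglobulin and complement, and section 2.8 compares the arms without baseline adjustment; confirm the baseline in Table 2, add one if absent, and adjust for it

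*Protocol article*

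**What the plan says.** Section 2.4.2 (Secondary outcome) opens with "Secondary outcomes will be measured individually at 6 weeks and 3 and 6 months post treatment". Item 2 of its list covers the immune assays: "milk and serum will be collected at each visit and the immunoglobulin (IgG, IgA, IgM) and the complement (C3, C4) will be detected". The same section refers the reader elsewhere for detail: "Table 2 has provided the time points and specific measurements of data". Table 2 is titled "Schedule of visits and assessments"; its contents were not available to this review.

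Section 2.5 (Adverse events) does use the word baseline. Tumour markers are tested "at baseline and 6 months", which implies, without saying so, that blood is drawn at entry.

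Section 2.8 (Statistical analysis) compares continuous outcomes between the arms with a two-tailed t test and names no covariate. Separately, "To assess changes of outcome levels over time", it plans repeated-measures ANOVA with post-hoc paired t tests or the Wilcoxon signed rank test.

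**The concern.** The cells come from a donor's umbilical cord, and safety is among the trial's stated aims. Section 2.4.2 gives no purpose for the immunoglobulin and complement assays, but an effect of the donor cells on the mother's immune values is the natural question for them to answer. If the only times are 6 weeks, 3 months and 6 months, three things follow.

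- **Change over time.** The repeated-measures analysis describes change only from 6 weeks onward. A shift that was complete by 6 weeks and then stable would not appear as within-woman change. Ordinary recovery after pregnancy, continuing past 6 weeks, would.
- **Precision and imbalance.** The arms are compared on raw laboratory values. Variation between women that a baseline value could explain stays in the error term, and a chance difference at entry passes into the result.
- **Individual cases.** If one woman has an abnormal complement value at 6 weeks, nothing shows whether it was already abnormal before the injection.

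A pre-injection value cannot be obtained once the injection has been given, unless baseline serum was stored.

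**Working it through.** **Does the text provide a baseline value?** Three statements bear on this.

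1. The opening sentence of section 2.4.2 lists post-treatment times only. It governs all secondary outcomes, including scar measurements that cannot exist before the incision.
2. The sampling rule in the same section is each visit. Visit is not defined in the text, so an entry visit could count. However, the rule covers milk and serum together, and milk collection fits the visits after delivery.
3. Section 2.5 says baseline explicitly for tumour markers; section 2.4.2 does not say it for the immune assays.

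The natural reading is that there is no baseline value, but only Table 2 can settle it.

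**What would a baseline value be worth?** The protocol gives no target difference or power for these assays, so it has no figure of its own to reproduce here.

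Inputs:
- 60 women per arm and 15% dropout (section 2.6), giving 60 × 0.85 = 51 evaluable per arm.
- Two-sided 0.05 (section 2.6), so z = 1.960.
- 80% power, z = 0.842. This is chosen for illustration; the 90% in section 2.6 is for the primary outcome.
- Correlation ρ between baseline and follow-up. It is not in the document and is assumed to be 0.3 to 0.7.

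Formula, in SD units: d = (1.960 + 0.842) × √(2/n) × √(1 − ρ²).

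With n = 51, √(2/51) = 0.198, so the unadjusted value is 2.802 × 0.198 = 0.555.

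| ρ (assumed) | Residual variance, 1 − ρ² | Detectable difference, 80% power | Power for 0.5 SD |
|---|---|---|---|
| none (unadjusted) | 1.00 | 0.55 SD | 71% |
| 0.3 | 0.91 | 0.53 SD | 75% |
| 0.5 | 0.75 | 0.48 SD | 83% |
| 0.7 | 0.51 | 0.40 SD | 94% |

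With no dropout (60 per arm), the unadjusted figure is 0.51 SD.

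**Chance imbalance.** The difference in baseline means between two randomized arms of 51 has standard error √(2/51) = 0.198 SD, so its 95% range is ±1.96 × 0.198 = ±0.39 SD. An imbalance at that limit carries ρ × 0.39 into the follow-up comparison: 0.19 SD at ρ = 0.5 and 0.27 SD at ρ = 0.7. The unadjusted t test allows for this in its error term on average, but in the trial as realized it cannot be seen or corrected without a baseline value.

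**The case against.** The strongest reply has three parts.

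**A baseline may be scheduled.** Section 2.4.2 defers to Table 2 and calls for serum at each visit, and the article shows a baseline contact at which data are recorded. A reader might infer from the quoted sentence that no woman has a pre-injection value. The documents do not support that as a flat statement. This part stands in full.

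**The comparison is randomized.** Under section 2.2, "In total, 120 participants will be randomly assigned to 1 of 2 groups in a 1:1 ratio", with concurrent saline as control. A reader might infer that an immune effect cannot be separated from each woman's own level. At group level that is wrong. Pre-existing levels are balanced in expectation, recovery after pregnancy common to both arms cancels, and a shift that had levelled off by 6 weeks would still show as a difference between arms at 6 weeks. This part stands for the group comparison. It does not answer the loss of precision, a chance imbalance in the trial as realized, or the reading of an individual woman's abnormal value.

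**The gain is uncertain and may be small.** Values taken in late pregnancy may correlate weakly with values at 6 weeks to 6 months. At ρ = 0.3 the detectable difference falls only from 0.55 to 0.53 SD. A reader might also infer that a real immune effect is likely to be missed; with no target difference stated, the documents cannot show that. This part limits the size of the point but does not remove it, because the change is cheap and individual interpretation does not depend on ρ.

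**Conclusion.** The point holds as one of precision and interpretability, not of bias. The text names only post-treatment times for the serum immune assays and plans an unadjusted between-arm test. On those times, the analysis of change begins 6 weeks after exposure. Whether a baseline value is scheduled must be confirmed in Table 2.

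Without baseline adjustment, the detectable difference is about 0.55 SD at 80% power, against 0.53 to 0.40 SD with it. This assumes 51 evaluable women per arm and correlations of 0.3 to 0.7 that the documents do not give. Without a pre-injection value, the trial also cannot tell whether an individual abnormality preceded the injection, whatever the correlation. The change is worth making because it costs little and the missing value generally cannot be recovered later.

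**What to change.** 1. **Check Table 2** for serum IgG, IgA, IgM, C3 and C4 at baseline.
2. **If none is scheduled,** assay them on serum taken before the injection, using the blood that baseline tumour-marker testing implies is drawn. Confirm that this draw does precede the injection. Milk stays post-delivery only.
3. **In either case,** replace the unadjusted t test in section 2.8 for these outcomes with a between-arm comparison at each later visit adjusted for the baseline value. ANCOVA per visit would do, or a mixed model across the three visits with arm-by-visit and baseline-by-visit terms.
4. **State the baseline in section 2.4.2,** so that it agrees with Table 2.
5. **List individual women** whose values move outside the reference range from a normal baseline.

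Section 2.9 says recruitment began in January 2017. Women already treated can gain a baseline value only if their entry serum was stored. Otherwise, a mixed model that treats baseline as one of the repeated measures, with a common baseline mean in both arms, keeps them in the analysis.

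Cost: at most one extra routine assay run per woman, 120 in total, and one line in the visit schedule. No new visit is needed if the baseline blood is drawn as implied. If Table 2 already has the baseline value, the change is to the analysis and the text only.

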**Table 2 T2:**
[figure not shown]
Schedule of visits and assessments.

### Adverse events

2.5

On the basis of clinical severity, all adverse events, including mild, moderate, and severe, will be obtained and recorded at baseline and throughout the 6-month follow-up. Every time when follow-up, the participants will come to the interviewing room where the case report form (CRF) with adverse events will be filled with their feedback and the specialist checks. We will focus on the wound infection, endometritis, or other infections occurring up to 6 months after delivery in both groups. To evaluate tumor formation as a delayed reaction, we will test the tumor markers (CA12–5, CA15–3, CA19–9, and carcinoembryonic antigen) at baseline and 6 months. The principal investigator (ZL) will be responsible for managing the adverse events clinically. All adverse events will be reported to the Adverse Events Monitoring Committee.

### Sample size

2.6

The sample size calculation is based on the primary outcome. According to previously published study, the proportion of uterine niche is 78% in women with a history of 1 cesarean delivery.^[17]^ We estimated a power of 90% and a 2-sided 0.05 level of significance, and a drop-out rate of 15% is taken into consideration. Finally, we plan to recruit 120 participants (60 in each group) would detect a 15% relative reduction in the primary outcome.

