#### Primary outcome

2.4.1

As a primary outcome of this clinical trial, we will evaluate the proportion of participants at 6 months who is found uterine niche in the uterus by transvaginal utrasonography.

The ultrasound examination will be performed using a 4 to 9 MHz convex transvaginal probe of Voluson E8 (General Electric Medical Systems, Chicago, IL). The niche is defined as a triangular anechoic area at the presumed site of incision.^[35]^ The standardized approach for imaging and measuring niche will be used as described in detail in a previous publication.^[12]^ Meanwhile, the following niche parameters, such as width of the triangular hypoechoic scar niche (W), depth of the triangular hypoechoic scar niche (D), length of the triangular hypoechoic scar niche (L), residual myometrial thickness (RMT), on the transection of the uterus will be also measured (Fig. 3). When the niche is not found, only the RMT value will be measured.

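### Sixty women per arm give about 26–30% power, not 90%, for the stated 15% relative reduction from 78%

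*Protocol article*

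**What the plan says.** The primary outcome is binary. Section 2.4.1 says "we will evaluate the proportion of participants at 6 months who is found uterine niche in the uterus by transvaginal utrasonography". Section 2.6 bases the sample size on this outcome and gives every input:

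- Control rate: "the proportion of uterine niche is 78% in women with a history of 1 cesarean delivery".
- Power, error rate and losses: "We estimated a power of 90% and a 2-sided 0.05 level of significance, and a drop-out rate of 15% is taken into consideration".
- Conclusion: "we plan to recruit 120 participants (60 in each group) would detect a 15% relative reduction in the primary outcome".

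Section 2.2 repeats the total of 120 and the 1:1 allocation. Section 2.8 names the chi-square or Fisher exact test for categorical outcomes, specifies intention to treat, and plans relative risks with 95% confidence intervals. No section gives another effect size or a design feature that would lower the number needed.

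**The concern.** Section 2.6 is the only justification given for the trial's size. An 11.7-point difference between two proportions near 70% normally needs several hundred women per arm, so 60 per arm at 90% power looks wrong at sight.

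The risk lies in interpretation. A reader who trusts the 90% will take a non-significant primary result as good evidence that the cells do not lower the niche rate by 15% in relative terms. If the real power is far lower, that inference fails. In addition, if the true effect is the stated one, a result that reaches significance will tend to overstate it.

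**Working it through.** **Inputs (section 2.6 unless noted)**

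- Control proportion p1 = 0.78.
- 15% relative reduction: p2 = 0.78 × 0.85 = 0.663, a difference of 0.117.
- Two-sided 0.05: z = 1.960. Power 90%: z = 1.2816.
- 60 per arm; with 15% drop-out, 60 × 0.85 = 51 evaluable.
- 1:1 allocation (section 2.2); chi-square comparison (section 2.8).

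**1. Trying to reproduce the plan's 60 per arm**

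Pooled two-proportion formula, with pm = (p1 + p2)/2:

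n = [1.960 × √(2 pm(1 − pm)) + 1.2816 × √(p1(1 − p1) + p2(1 − p2))]² / (p1 − p2)²

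- pm = 0.7215; √(2 × 0.7215 × 0.2785) = 0.6339.
- √(0.78 × 0.22 + 0.663 × 0.337) = 0.6285.
- n = (1.2425 + 0.8055)² / 0.117² = 306.4, so 307 evaluable per arm.
- Drop-out: 307 / 0.85 = 361.2, so 362 per arm and 724 in total.

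The plan's figure is not reproduced; 724 is about six times 120.

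**2. Power at the planned size**

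Power = Φ{[(p1 − p2)√n − 1.960 × 0.6339] / 0.6285}

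- n = 51: Φ(−0.647) = 25.9%.
- n = 60: Φ(−0.535) = 29.6%.

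Exact enumeration of the chi-square test gives 26.4% and 30.6%. Arcsine, unpooled and log relative risk approximations give 25.6–26.4% and 29.3–30.2%.

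**3. Other readings of the sentence**

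| Reading | Recruited in total, with drop-out | Power at the planned size |
|---|---|---|
| 15 points absolute (78% to 63%), 90% power, two-sided | 456 | 38% (51 per arm), 44% (60 per arm) |
| 15% relative, 80% power, one-sided | 426 | 37% (51), 41% (60) |
| 120 taken as the number per arm, 15% relative, two-sided | – | 46% (102 per arm), 52% (120 per arm) |

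None of these gives 120 women at the stated power.

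**4. What 60 per arm can detect**

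Solving the power formula for p2 with p1 = 0.78, two-sided 0.05:

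| Power | 51 evaluable per arm | 60 per arm |
|---|---|---|
| 90% | 47.6% (30.4 points, 39% relative) | 50.1% (27.9 points, 36% relative) |
| 80% | 51.8% (26.2 points, 34% relative) | 54.0% (24.0 points, 31% relative) |

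**5. What a non-significant result could say**

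The standard error of the log relative risk is √[(1 − p1)/(n p1) + (1 − p2)/(n p2)]. Take 51 per arm and 78% observed in the control arm.

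- Observed relative risk 0.85: standard error 0.1245; 95% interval about 0.67 to 1.08. The planned effect, observed exactly, is not significant.
- Observed relative risk 1.00: standard error 0.1052; interval about 0.81 to 1.23. A 15% reduction (0.85) is inside; reductions above about 19% are outside.
- Observed relative risk 1.05: standard error 0.0993; interval about 0.86 to 1.28. A 15% reduction is now outside.

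For scale, if 40 of 51 control women have a niche (78%), chi-square significance needs 30 or fewer of 51 in the cell arm, an observed relative reduction of 25%.

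**The case against.** Four points on the other side deserve weight.

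- **The 26% is the lower end.** It assumes that the full 15% drop-out occurs and that only women with a scan count. Section 2.8 specifies intention to treat, and 15% is a planning allowance. This stands, so the fair statement is about 26–30%. It does not bring the figure near 90%.
- **A null result is not empty.** A reader might infer from such low power that a non-significant result would tell us almost nothing. The plan's own figures do not support that: equal rates in the two arms would exclude relative reductions above about 19%. Nor is it true that every non-significant result leaves a 15% reduction open, since an observed relative risk of about 1.05 excludes it. The point that holds is that non-significance alone is not evidence against 15%.
- **The faulty input is unknown.** The article does not show whether the number of women, the effect size, the power or the word relative is wrong. This stands. For that reason the 30-point fall can be reported only as what 120 women can detect; nothing in the article supports it as the expected or intended effect.
- **Overestimation is conditional.** A significant result would tend to exaggerate if the true effect is the stated 11.7 points. It need not if the true effect is about 30 points.

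The condensed form of a journal article is no defence here, because section 2.6 gives every input and then draws a conclusion that does not follow from them.

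**Conclusion.** Section 2.6 is wrong as written and must be corrected. For the effect it names, the trial has about 26–30% power instead of 90%; the recruitment needed for 90% is about 724, not 120. If the 15% was meant as percentage points, power is still only 38–44%.

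The figures rest on the article's 78% control rate, a two-sided 0.05 test of two independent proportions, and between 51 and 60 women per arm analysed. The choice of approximation changes the power at the stated effect by about one percentage point.

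For interpretation, a non-significant result could not by itself be taken as evidence against a 15% relative reduction, but its confidence interval could argue against much larger ones.

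**What to change.** Keep 120 women and correct the statement in section 2.6:

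- Delete the claim that 120 women give 90% power for a 15% relative reduction.
- State instead, for a 78% control rate and two-sided 0.05: 90% power for a fall to about 48% with 51 evaluable per arm, or about 50% with 60; 80% power for a fall to about 52% or 54%; and about 26–30% power for a 15% relative reduction.
- Label these as detectable effects at the planned size, not as a new target effect.
- Add that a non-significant primary result will be interpreted from the 95% confidence interval for the relative risk already planned in section 2.8, and not from the 90% figure.

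The cost is wording, plus a less favourable power statement. No extra women are needed, and the primary outcome and its analysis do not change.

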### Data management and monitoring

2.7

All researchers will be given complete good clinical practical training. They will independently assess the effects of the interventions and collect the data. Both paper and electronic versions of the CRF will be kept in the secure research archives at the Southern Medical University Affiliated Maternal & Child Health Hospital of Foshan for 10 years. The principal investigator will be responsible for the confidential clinical information. Data monitoring committee, which comprises an epidemiologist, a statistician, and an obstetrician, will responsible for reviewing the results. They have the right to decide whether the trial should continue.

### Statistical analysis

2.8

For data analysis, all analyses will be performed according to the intention-to-treat principle. Continuous data will be expressed as mean/standard deviation if it meets normal distribution, otherwise it will be presented by medians/interquartile range; categorical data will be expressed as frequency and percentage. In terms of comparison between the 2 groups, 2-tail Student *t* test for continuous data or the Chi-square test or Fisher exact test for categorical data will be used for outcomes. Relative risks and 95% confidence intervals will be calculated for outcomes. To assess changes of outcome levels over time, an analysis of variance (ANOVA) for repeated measures with post-hoc paired *t* tests or Wilcoxon signed rank test will be used for continuous data. Statistical significance is established at *P* < .05. Statistical analysis will be performed using R 3.0.3.

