## Abstract

**Background::**

Uterine niche is defined as a triangular anechoic structure at the site of the scar or a gap in the myometrium at the site of a previous caesarean section. The main clinical manifestations are postmenstrual spotting and intrauterine infection, which may seriously affect the daily life of nonpregnant women. Trials have shown an excellent safety and efficacy for the potential of mesenchymal stem cells (MSCs) as a therapeutic option for scar reconstruction. Therefore, this study is designed to investigate the safety and efficacy of using MSCs in the treatment for the uterine niche.

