### Participants

2.1

Primiparous women with a singleton pregnancy between the 37th and 42nd week of gestation will be eligible for inclusion if they are aged 21 to 35 years. Gestational age will be estimated in accordance with the guidelines of the American College of Obstetricians and Gynecologists.^[34]^ Participants will come from our maternity clinic. Obstetricians will answer for the information, details, and requirements of the trial. We will exclude participants who met one of the following criteria: multiple gestation, placenta abruption, placenta previa, fibroids, antepartum hemorrhage, preeclampsia/eclampsia, hepatic or renal dysfunction, any systemic uncontrolled disease or inability to provide consent. After being screened for inclusion and exclusion criteria (Table 1), eligible participants will be introduced in the trial. Each eligible participant must provide their informed consent, and then randomly allocated to MSCs or placebo group according to a randomization numbers. Through the interview, the assistant researchers will be responsible to assess and record the participants’ baseline data.

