### Procedures

2.3

On the basis of previous preclinical safety and bioactivity analyses, participants will be randomly assigned to receive direct intramuscular injection of MSCs (a dose of 1∗10^7^ cells in 1 mL of 0.9% saline) (MSCs group) or an identical-appearing 1 mL of 0.9% saline (placebo-controlled group).

Cesarean procedures and care followed usual practices. All participants will be performed by obstetricians from our department using a unified double-layer uterine closure technique with a continuous absorbable polyglycolic 1–0 suture. After suturing the uterine incision, direct local intramuscular injection will be performed in the uterine incision as soon as possible on the operating table. One milliliter will be injected as 20 aliquots of 0.05 mL into each injection site on the incision using 23-gauge needles. Injection sites will be selected near the incision at evenly 20 different sites (Fig. 2).

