**Figure 2 F2:**
[figure not shown]
Direct intramuscular injection sites. (A) Real scene showing injection sites; (B) Schematic drawing showing injection sites. Injection sites will be selected near the incision at evenly 20 different sites.

The MSCs are obtained from the umbilical cord of a healthy donor after delivery. All donors must be provided written informed consent. All procedures for cell processing are carried out according to Good Manufacturing Practice from Health-Biotech Pharmaceutical Company (Guangzhou, China).

MSCs release criteria for clinical use will be as follows: absence of pathogen contamination (bacterial, fungal, viral, or mycoplasma); viability >80% as evaluated by trypan blue staining; immune phenotype, showing the expression of CD73, CD90, and CD105 (Src homology-2) surface molecules (95%); and absence of CD45, CD34, CD11b, CD19, and HLA-DR markers (<2%).

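### Section 2.8 puts all analyses, read literally including adverse events, under intention-to-treat, which can dilute an MSC harm contrast if some women are not injected as assigned

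*Protocol article*

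**What the plan says.** Section 2.8 (Statistical analysis) opens with a blanket rule: "For data analysis, all analyses will be performed according to the intention-to-treat principle". No later sentence narrows it, and no safety or as-received population is named elsewhere in the article.

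Safety is a declared aim. The abstract says that "this study is designed to investigate the safety and efficacy of using MSCs in the treatment for the uterine niche". Section 2.5 (Adverse events) says that all adverse events "will be obtained and recorded at baseline and throughout the 6-month follow-up", and adds: "We will focus on the wound infection, endometritis, or other infections occurring up to 6 months after delivery in both groups". It also plans tumour markers at baseline and 6 months. It does not say whether the groups are those assigned or those actually treated.

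Allocation and exposure are separate steps. In section 2.1, "Each eligible participant must provide their informed consent, and then randomly allocated to MSCs or placebo group". In section 2.3, "After suturing the uterine incision, direct local intramuscular injection will be performed in the uterine incision as soon as possible on the operating table". Section 2.3 also lists conditions that the cells must meet before use.

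**The concern.** Grouping by assignment is cautious for efficacy, because deviations shrink the apparent benefit. For harm the same shrinkage favours the product. A woman allocated to MSCs but never injected adds to the MSC denominator without exposure. If she had been given saline in error, her events would still count as MSC events; a placebo woman given cells in error would have any cell-related event counted under placebo.

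The trial has 60 women per group and describes itself as the first of its kind in this use. Few events of any one type can be expected, so the denominator and the attribution of individual events matter. This is also more than a detail left for an analysis plan: the article states a rule, and an as-received safety set in a later plan would sit awkwardly with its wording.

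**Working it through.** **Inputs from the protocol article.** 60 women per group (sections 2.2 and 2.6). One injection, during surgery (2.3). Intention-to-treat for all analyses (2.8).

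**Inputs not in the article, so assumed.** The share not injected (u), the share given the other product (c), and the event risks. Uninjected women and women given saline are taken to carry the same background risk.

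**The plan's own figure.** There is none to reproduce: the article gives no number for the adverse-event comparison. The 15% in section 2.6 is drop-out, not non-injection.

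**1. Non-injection.** Let pt be the event risk after MSCs and pc the background risk. The as-assigned risk in the MSC arm is (1-u)·pt + u·pc. Subtracting pc gives

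as-assigned risk difference = (1-u)·(pt - pc).

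Illustration with pc = 5% and pt = 15% (difference 10.0 points, relative risk 3.0). Power is for a two-sided 0.05 test. The last column keeps only injected women, with the same share uninjected in both arms.

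| u | As-assigned difference | As-assigned relative risk | Power as assigned, 60 per arm | Power in injected women, 60(1-u) per arm |
|---|---|---|---|---|
| 0 | 10.0 points | 3.00 | 45% | 45% |
| 5% | 9.5 | 2.90 | 42% | 43% |
| 10% | 9.0 | 2.80 | 39% | 41% |
| 15% | 8.5 | 2.70 | 36% | 39% |

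The proportional shrinkage of the difference does not depend on the risks chosen. With 10% against 20%, u = 10% again turns 10.0 points into 9.0, and the relative risk falls from 2.00 to 1.90.

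**2. Product mix-up.** If a share c of each arm receives the other product, the as-assigned difference is (1-2c)·(pt - pc). With pc = 5% and pt = 15%:

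- 1 woman per arm: (1 - 2/60) × 10 = 9.7 points, relative risk 2.87
- 2 per arm: 9.3 points, relative risk 2.75
- 3 per arm: 9.0 points, relative risk 2.64

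**3. Zero-event bound.** If no event of a given type is seen in n women, the one-sided 95% upper bound on its risk is 1 - 0.05^(1/n).

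- n = 60 (all assigned): 1 - 0.05^(1/60) = 4.9%
- n = 54 (10%, or 6 women, not injected): 1 - 0.05^(1/54) = 5.4%

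The article does not plan such a bound. It is used here only to show the size of the effect.

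**4. No deviations.** With u = 0 and c = 0, the as-assigned and as-received summaries are identical.

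**The case against.** The strongest reply is that nothing in the article shows that any woman will be treated other than as assigned. Without deviations there is no dilution. Intention-to-treat is also unbiased for the effect of assignment; the dilution concerns the effect of receiving the cells. Both statements are correct, so the point has to be conditional.

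A second reply concerns scope. Section 2.5 sets no analysis set, and the tests in 2.8 are described as applying to outcomes, which section 2.4 lists apart from adverse events. A safety set could be defined in an analysis plan that is not shown. This weakens the reading that adverse events are covered but does not remove it, because the opening sentence of 2.8 speaks of all analyses.

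A reader might also infer more than the article supports:

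- **That a failed cell release will leave allocated women uninjected.** Section 2.3 lists release criteria but does not say they are checked after randomisation. Section 2.1 puts allocation after consent without timing it against surgery. Sealed envelopes and a pharmacist preparing the product (2.2) fit allocation shortly before surgery.
- **That women lost to follow-up count as event-free.** Intention-to-treat fixes the group in which a woman is counted. It does not say how missing follow-up is handled, and the article gives no rule on that.
- **That drop-out widens the gap.** Subtracting 9 drop-outs as well (15% of 60) gives 60 - 6 - 9 = 45 and a bound of 6.4%. The extra step reflects missing follow-up, not the analysis set, and it assumes that no uninjected woman is also a drop-out.
- **That immunoglobulin and complement belong with safety.** Section 2.4.2 declares them secondary outcomes, so they should stay under the intention-to-treat rule.

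Finally, the effect is modest. In the illustration, power is only 45% with no deviations at all, so the sample size limits the detection of harm far more than the analysis set does. That stands, and it sets the severity.

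**Conclusion.** The point holds in a limited, conditional form. The blanket sentence in 2.8 is worded too broadly for a trial that names safety as an aim, and applying it literally to adverse events can dilute a harm contrast.

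The excess risk shrinks by the non-injected share: 5 to 15% if 5 to 15% of the MSC arm is not injected. At 10%, the zero-event bound differs by half a percentage point (4.9% against 5.4%). These rates are assumptions, as is background risk in uninjected women.

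A reader might conclude that the plan makes MSCs look safer than they are. The article does not support that: it gives no deviation rate, and the bias is zero if every woman is injected as assigned. The severity is minor, and the correction is a cheap improvement.

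**What to change.** In section 2.8, limit the intention-to-treat rule to the efficacy outcomes and the declared secondary outcomes, including immunoglobulin and complement. Add that adverse events and tumour markers will be summarised among women who received an injection, grouped by the product received, with the number assessed reported. Show the as-randomised table beside it.

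The cost is one sentence and one additional safety table. The downside is that the safety groups are no longer strictly the randomised groups; the as-randomised table covers this. Reporting the number assessed also lets readers see how many women were lost, since a loss could itself be related to an adverse event.
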